## **3. Study Design**

This study is a randomized controlled non-inferiority clinical trial conducted at Xiamen University Zhongshan Hospital, which will be registered at Chinese Clinical Trial Registry (ChiCTR) prior to participant enrollment. The study groups include the control group and the experimental group. The trial consists of screening period and treatment period.

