### **3.2 Treatment Period**

(1) Control Group: 8 mg of dexamethasone is administered intravenously 0.5 hours before chemotherapy, and 1 tablet of netupitant and palonosetron hydrochloride capsules (each containing 0.3 g of netupitant and 0.5 mg of palonosetron hydrochloride) is taken orally 1 hour before chemotherapy.

(2) Experimental Group: 5 mg of dexamethasone is administered intravenously 0.5 hours before chemotherapy, and 1 tablet of netupitant and palonosetron hydrochloride capsules (each containing 0.3 g of netupitant and 0.5 mg of palonosetron hydrochloride) is taken orally 1 hour before chemotherapy.

Stratification Factors: Gender, age, patient's risk factors for CINV, ECOG score, tumor type, distant metastasis of the tumor, emetogenic risk of the chemotherapy regimen, smoking history, and drinking history, etc.

Drug Discontinuation Criteria During Treatment: Subjects should discontinue the drug if they experience severe adverse events or specific types of adverse events, such as severe drug intolerance or allergic reactions.

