# **10 Data Analysis and Statistical Methods**

## **10.1 Sample Size Estimation**

Based on previous studies of 8-12 mg DEX plus NEPA for CINV prevention [8,10], a CRR of 80% was assumed for the control group (8D DEX group). The non-inferiority margin was set at 15%. For the sample size calculation, the CRR in the experimental group (5D DEX group) was also assumed to be 80% under the null hypothesis of non-inferiority. Using a normal approximation method for non-inferiority testing of proportions (Z-test, unpooled, one-sided  $\alpha=0.05$ , power=80%), a total of 176 participants (88 per group) was calculated to be sufficient to demonstrate non-inferiority. To account for a potential 5% attrition rate, the enrollment was increased to 186 participants (93 per group). The sample size calculation was performed using PASS 2021 software.

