### 10.5 General Principles for Efficacy Analysis

In this study, unless otherwise specified, efficacy data will be descriptively summarized according to the following general principles:

- Demographic and clinical characteristics were analyzed using descriptive statistics, with categorical variables expressed as frequencies (percentages) and continuous variables as median (interquartile range).

- The efficacy endpoints (CRR, TCR, and CCR) were analyzed for noninferiority using a stratified Mantel-Haenszel approach to compare dose cohorts, adjusting for age. The combined risk difference and its two-sided 95% confidence interval were calculated. Noninferiority was concluded if the lower confidence limit exceeded the pre-specified margin of -15%. Changes in response within subjects across different treatment phases were assessed using McNemar's test. P values for noninferiority tests were reported as one sided, whereas other P values were two sided.
- Group comparisons employed chi-square/Fisher's exact tests for binary variables, Mann-Whitney U test for continuous variables, and Kruskal-Wallis test for multicategorical data.

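### Section 10.5 sends every group comparison of a variable with more than two categories to Kruskal-Wallis; for unordered categories the p-value then depends on arbitrary codes

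*Protocol*

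**What the plan says.** The last bullet of Protocol section 10.5 fixes one test for each type of variable:

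- Two categories: "Group comparisons employed chi-square/Fisher's exact tests for binary variables".
- Continuous: "Mann-Whitney U test for continuous variables".
- More than two categories: "Kruskal-Wallis test for multicategorical data".

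The section does not restrict the third line to ordered categories, and no other section sends unordered variables elsewhere. Only two arms are compared; in section 3, "The study groups include the control group and the experimental group".

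Section 3.2 lists patient and disease characteristics as stratification factors, among them "ECOG score, tumor type, distant metastasis of the tumor". Of these, tumour type is plainly unordered with several levels. ECOG score is limited to 0 or 1 by the inclusion criteria, and emetic risk to moderate or high, so those two are binary in this trial.

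The first bullet of section 10.5 says that demographic and clinical characteristics are summarised descriptively, with categorical variables as counts and percentages.

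**The concern.** Kruskal-Wallis is a rank test. Comparing two arms on a categorical variable with it means turning the categories into numbers, ranking the patients on those numbers and comparing mean ranks. With two arms this is the Mann-Whitney test.

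If the categories have a natural order, the numbers carry that order and the test answers a sensible question: whether one arm tends towards higher categories. If they have none, the numbers are labels chosen when the database was built. Relabelling the categories changes the ranks and the p-value while the data stay the same.

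Because the rule reserves chi-square and Fisher for binary variables, the test that would suit a multi-level nominal variable is excluded by the text. At stake is the meaning of any p-value reported for such a variable. In an open-label study a result that can be moved by a coding choice is also better removed in advance.

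**Working it through.** **Inputs.** 93 patients per arm (section 10.1) and two arms (section 3). The protocol gives no tumour-type counts, so the counts below are assumptions.

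**The plan's own figure.** The arm size reproduces. With 80% response in both arms, margin 0.15, one-sided alpha 0.05 and 80% power, n = 2 × 0.8 × 0.2 × (1.645 + 0.842)² / 0.15² ≈ 88 per arm, 176 in total. Then 176 / 0.95 = 185.3, rounded up to 186, or 93 per arm. The present point disputes none of this.

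**Assumed table.** Four unordered categories A, B, C, D: 30/22/10/31 in one arm and 20/36/18/19 in the other. Column totals are 50, 58, 28, 50, so the expected counts per arm are 25, 29, 14, 25.

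**Chi-square.** 2 × (5²/25 + 7²/29 + 4²/14 + 6²/25) = 2.000 + 3.379 + 2.286 + 2.880 = 10.545 on 3 degrees of freedom, p = 0.014. The value is the same however the categories are labelled.

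**Kruskal-Wallis.** With two equal arms and N = 186, H = (12/187) × d² / T. Here d is the distance of the first arm's mean rank from 93.5, and T is the tie correction, 1 − Σ(t³ − t)/(N³ − N) = 1 − 466,878/6,434,670 = 0.927.

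| Order given to the codes | Mean rank, first arm | d | H | p |
|---|---|---|---|---|
| A, B, C, D | 8745.5/93 = 94.04 | 0.54 | 0.020 | 0.89 |
| C, B, A, D | 9761.5/93 = 104.96 | 11.46 | 9.09 | 0.003 |

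These are the two extremes of the 24 codings. There are 12 distinct p-values; 8 of the 24 codings give p at or below 0.05 and 16 give p above it.

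**Other assumed tables, 93 per arm.**

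| Counts | Chi-square p | Kruskal-Wallis p over 24 codings |
|---|---|---|
| 40/25/18/10 vs 28/33/14/18 | 0.111 | 0.018 to 0.927 |
| 40/25/18/10 vs 35/28/16/14 | 0.732 | 0.295 to 0.985 |
| 40/13/30/10 vs 25/28/15/25 | 0.00014 | 0.00002 to 0.882 |

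The error can run in either direction. In the nearly balanced table no coding reaches 0.05, though the p-value still moves widely.

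**Equivalence with two arms.** For the first of these tables, coded in the listed order, Kruskal-Wallis and Mann-Whitney (without continuity correction) both give p = 0.0936.

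**The case against.** **The protocol does not name tumour type as a tested variable.** This stands. The bullet on group comparisons lists types of variable, not variables, and clinical characteristics are to be described. Tumour type is only an example of what the rule would cover if it were compared.

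**A reader might infer that baseline imbalance will be judged by an arbitrary p-value.** The inference is tempting because section 3.2 lists tumour type as a stratification factor while section 10.2 describes a single unstratified random list. The documents do not support it. They prescribe no balance test, no threshold and no action that depends on one, and the counts and percentages would show any imbalance directly. The mismatch between sections 3.2 and 10.2 is a separate matter.

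**The clause may have been meant for ordered categories,** such as the severity grades in section 8.4.2. For those the test is legitimate. The wording does not say so, however. It states a rule for all multi-category data rather than leaving a detail open for a statistical analysis plan to fill.

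**Used the other way round, the test is harmless.** With the categories as groups and a binary variable as response, H equals (N − 1)/N times Pearson's chi-square (here 10.545 × 185/186 = 10.488) and the labels do not matter. But the sentence concerns comparisons between study groups, so this is not its natural reading.

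**The counts are invented.** They are, and the ranges say nothing about what this trial's data will show. The dependence on coding is a property of ranking labels and does not rest on the chosen counts.

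**Conclusion.** The rule is wrong as written for unordered variables with more than two levels and right for ordered ones. The fault is the missing distinction between nominal and ordinal data.

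The consequence is minor and conditional: it arises only if a nominal multi-level variable is tested between the arms. In that case the p-value has no fixed value; in the main illustration it runs from 0.003 to 0.89 against a chi-square p of 0.014, on assumed counts.

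A reader might go further and suppose that the trial's main result is exposed. It is not. The complete response, total control and complete control rates are binary and are analysed by the age-stratified Mantel-Haenszel risk difference, into which no p-value from this clause enters. Sample size is also unaffected.

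**What to change.** Reword the last bullet of section 10.5 so that the test follows the scale of the variable:

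- Nominal with more than two levels: chi-square, or Fisher-Freeman-Halton when expected counts are small.
- Ordinal: Mann-Whitney (equivalent to Kruskal-Wallis with two arms) or a trend test.
- Binary and continuous variables: as now.

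The cost is one line of text. The tests run in the software already named; data collection and sample size do not change.

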## 10.6 General Principles for Safety Analysis

Safety analysis includes:

- Analysis of patient discontinuation, dose reduction, or suspension due to adverse events;
- Incidence and severity of adverse events;
- Analysis of the relationship between adverse events and the drug;
- Analysis of the outcomes of adverse events;
- Analysis of serious adverse events;
- Descriptive statistical summary of laboratory, vital signs, and electrocardiogram data;
- Incidence of abnormal laboratory indicators;
- Analysis of positive abnormal changes in laboratory indicators, vital signs, and other data compared to baseline.

## 11 Dropout of Subjects

All subjects who have signed the informed consent form and are screened as eligible to enter the trial have the right to withdraw from the study at any time. Subjects

who withdraw for any reason before completing the clinical trial and cannot be evaluated for safety and efficacy are considered dropouts (subjects who withdraw due to disease progression with clear medical evidence after enrollment are not considered dropouts). When a subject drops out, the investigator must record the reason for dropout in the CRF, complete all possible assessment items, and carefully document the last visit record in the CRF. For subjects who drop out due to adverse reactions and are finally determined to be related to the study drug after follow-up, this should be recorded in the CRF and notified to the investigator. Subjects who only underwent screening but did not receive a drug number and withdrew from the study are not considered dropouts. All enrolled subjects with at least one medication record will be included in the safety set and should be analyzed in the safety evaluation.

Subjects who withdraw from the study cannot re-enter the study, and their numbers cannot be reused.

## **12 Study Timeline**

- Enrollment of the first subject: October 2024
- Estimated enrollment of the last subject: August 2025
- Estimated study completion date: August 2025

## Appendix 1: ECOG Performance Status Scale (Eastern Cooperative Oncology Group)

Patients should be evaluated for general health status before treatment. An important indicator of general health status is the evaluation of performance status (PS). Performance status is an indicator of a patient's general health status and ability to tolerate treatment based on their physical strength. The Eastern Cooperative Oncology Group (ECOG) developed a simplified performance status score table, as shown in the table below:

| ECOG performance status scoring criteria |                                                                                                                                                           |
|------------------------------------------|-----------------------------------------------------------------------------------------------------------------------------------------------------------|
| GRADE                                    | ECOG PERFORMANCE STATUS                                                                                                                                   |
| 0                                        | Fully active, able to carry on all pre-disease performance without restriction                                                                            |
| 1                                        | Restricted in physically strenuous activity but ambulatory and able to carry out work of a light or sedentary nature, e.g., light house work, office work |
| 2                                        | Ambulatory and capable of all selfcare but unable to carry out any work activities; up and about more than 50% of waking hours                            |
| 3                                        | Capable of only limited selfcare; confined to bed or chair more than 50% of waking hours                                                                  |
| 4                                        | Completely disabled; cannot carry on any selfcare; totally confined to bed or chair                                                                       |
| 5                                        | Dead                                                                                                                                                      |

## Appendix 2: NCCN Emetic Risk Classification for Anticancer Agents

| EMETOGENIC POTENTIAL OF PARENTERAL ANTICANCER AGENTS   |                                                                                                                                                                                                                                                                                                                                                                                                                                                                                       |                                                                                                                                                                                                                                                                                                                                                                                                                    |                                                                                                                                                                                                                                                                                                                       |
|--------------------------------------------------------|---------------------------------------------------------------------------------------------------------------------------------------------------------------------------------------------------------------------------------------------------------------------------------------------------------------------------------------------------------------------------------------------------------------------------------------------------------------------------------------|--------------------------------------------------------------------------------------------------------------------------------------------------------------------------------------------------------------------------------------------------------------------------------------------------------------------------------------------------------------------------------------------------------------------|-----------------------------------------------------------------------------------------------------------------------------------------------------------------------------------------------------------------------------------------------------------------------------------------------------------------------|
| LEVEL                                                  | AGENT                                                                                                                                                                                                                                                                                                                                                                                                                                                                                 |                                                                                                                                                                                                                                                                                                                                                                                                                    |                                                                                                                                                                                                                                                                                                                       |
| High emetic risk
(>90% frequency of emesis)         | 
 
• AC combination defined as any chemotherapy regimen that contains an anthracycline and cyclophosphamide
 
• Carboplatin AUC <math>\geq 4</math>
 
• Carmustine >250 mg/m^2
 
                                                                                                                                                                                                                              | 
 
• Cisplatin
 
• Cyclophosphamide >1500 mg/m^2
 
• Dacarbazine
 
• Doxorubicin <math>\geq 60</math> mg/m^2
 
• Epirubicin >90 mg/m^2
 
• Fam-trastuzumab deruxtecan-nxki
 
                                                                                                                   | 
 
• Ifosfamide <math>\geq 2</math> g/m^2 per dose
 
• Mechlorethamine
 
• Melphalan <math>\geq 140</math> mg/m^2
 
• Sacituzumab govitecan-hziy
 
• Streptozocin
 
                                                      |
| Moderate emetic risk
(>30%–90% frequency of emesis) | 
 
• Aldesleukin >12–15 million IU/m^2
 
• Amifostine >300 mg/m^2
 
• Bendamustine
 
• Busulfan
 
• Carboplatin AUC <4
 
• Carmustine <math>\leq 250</math> mg/m^2
 
• Clofarabine
 
• Cyclophosphamide <math>\leq 1500</math> mg/m^2
 
• Cytarabine >200 mg/m^2
 
• Dactinomycin
 
• Daunorubicin
 
 | 
 
• Dinutuximab
 
• Doxorubicin <60 mg/m^2
 
• Dual-drug liposomal encapsulation of cytarabine and daunorubicin
 
• Epirubicin <math>\leq 90</math> mg/m^2
 
• Idarubicin
 
• Ifosfamide <2 g/m^2 per dose
 
• Irinotecan
 
• Irinotecan (liposomal)
 
• Lurbinectedin
 
 | 
 
• Melphalan <140 mg/m^2
 
• Methotrexate <math>\geq 250</math> mg/m^2
 
• Mirvetuximab soravtansine-gynx
 
• Naxitamab-gqgk
 
• Oxaliplatin
 
• Romidepsin
 
• Temozolomide
 
• Trabectedin
 
 |

Table framework is based on the emetogenicity classifications described in the following publications: Hesketh PJ, et al. J Clin Oncol 1997;15:103-109. Grunberg SM, et al. Support Care Cancer 2011;19:S43-S47.

### Appendix 3: Serious Adverse Event (SAE) Report Form

(Standardized template based on ICH-GCP guidelines)

|                                      |                                                                                                                                                  |         |                             |              |
|--------------------------------------|--------------------------------------------------------------------------------------------------------------------------------------------------|---------|-----------------------------|--------------|
| Report Type                          | __Initial __Follow-up __Final                                                                                                                    |         | Report Date: Year Month Day |              |
| Medical Institution & Specialty Name |                                                                                                                                                  |         | Telephone                   |              |
| Reporting Unit Name                  |                                                                                                                                                  |         | Telephone                   |              |
| Investigational Drug Name            | Chinese Name:                                                                                                                                    |         |                             |              |
|                                      | English Name:                                                                                                                                    |         |                             |              |
| Drug Category                        | __Traditional Chinese Medicine
__Chemical Drug __New Biological Product
__Radiopharmaceutical
__Imported Drug __Others                  |         |                             | Class II     |
| Clinical Research Phase              | __Phase I __Phase II __Phase III
__Phase IV
__Bioequivalence Trial __Clinical Verification                                                 |         |                             | Dosage Form: |
| Subject Information                  | Name:                                                                                                                                            | Gender: | Date of Birth:              | Ethnicity:   |
|                                      | Disease Diagnosis:                                                                                                                               |         |                             |              |
| SAE Details                          | __Hospitalization __Prolonged Hospital Stay __Disability
__Functional Impairment
__Congenital Anomaly __Life-threatening or Death __Others |         |                             |              |
| SAE Occurrence Time:                 | SAE Severity: __Mild __Moderate __Severe                                                                                                         |         |                             |              |

